#### **13.4.2. Secondary endpoint analyses**

##### **13.4.2.1. Efficacy**

Systemic 11 $\beta$ -HSD1 activity and skin function analyses will be conducted as for the primary endpoint (above). The strength of association between skin AZD4017 at day 28 concentration and plasma AZD4017 at day 35 in the active treatment arm will be assessed using Pearson's product moment correlation coefficient; for severely skewed variables for which a suitable transformation cannot be found, Spearman rank correlation will be used. For all correlation analyses, absolute correlation coefficients with a value of  $r(ho) \geq 0.3$  will be considered preliminary evidence of substantive association.

##### **13.4.2.2. Safety**

Safety analyses will be conducted in all patients who received any study treatment, according to treatment received. Continuous safety variables (BMI, waist-hip ratio, BP, HbA1c levels, lipids, FBC, LFT, eGFR, U+E, adrenal and thyroid function test) will be summarized descriptively by patient group at each timepoint. Unadjusted and adjusted summaries (adjusted for gender, age and baseline HbA1c) for absolute values and changes from baseline will be presented; between-group differences in absolute values and changes from baseline will be presented together with 90% confidence intervals. Adjusted summaries will be obtained via a linear regression model which mirrors analysis of covariance. Where necessary, transformations to a normal distribution will be performed. Where applicable, numbers of patients in each group whose values exceeded ULN (or were below the lower limit of normal) during the trial will be presented, corrected for exposure by 100 patient years.

Line listings of all AEs will be provided in the end of trial report. The frequency of all AE during the study period will be presented for each treatment group separately within classes of AEs defined by CTCAE preferred term. The data will be displayed as number of subjects experiencing the AE, percentage of subjects, and number of AE. AE will also be summarized by severity and relation to IMP. For recurrent AEs, the most severe occurrence will be recorded per AE per patient. AE data will also be corrected for exposure by 100 patient-years. For expected AEs the recorded rates will be compared against the rates outlined in the IB.

In addition to the above, the proportions of patients who passed the overall assessment of blood safety will be summarised using absolute and relative frequencies at each visit, in all patients and by treatment group at days 0, 7, 28, 35 & 42.

No inferential testing will be conducted; safety will be assessed in terms of the clinical relevance of the AEs reported and of any observed differences between groups.

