7) Alanine aminotransferase (ALT) and/or aspartate aminotransferase (AST) and/or alkaline phosphatase (ALP) > 1.5x upper limit of normal (ULN)

8) Bilirubin (total) > 1.5x ULN

9) An eGFR calculated by the Modification of Diet in Renal Disease equation of <45 ml/min/m^2

10) Creatine kinase (CK) >2 x ULN

11) Participant is, at the time of signing the informed consent, a user of recreational or illicit drugs (including marijuana) or has had a recent history (within the last year) of drug or alcohol abuse or dependence on questioning or clinical history

12) Receiving any topical, systemic (including vaginal/rectal) or inhaled GC treatment at the time of or within 3 months prior to the screening visit

13) Taking any anticoagulant medication (blood thinning e.g. warfarin)

14) Taking probenecid or similar (for gout) at the time of inquiry

15) Any medical/surgical procedure (excluding skin biopsies) or trauma during IMP administration or within one week following the last administration of the IMP as judged by the CI

16) Involved in the planning and/or conduct of the study (applies to both AstraZeneca staff and/or staff at the study site)

17) Participated in any other clinical study within 1 calendar month prior to the screening visit (except registry-only participation)

18) Deemed otherwise inappropriate to participate by the trial team

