### 8.6. Special warnings and precaution for use

AZD4017 has been studied in healthy human volunteers some patient groups and is generally well tolerated.

The most commonly reported AE amongst healthy volunteers were gastrointestinal disorders and headache and were of mild to moderate intensity. Please refer to IB for more information.

In a multiple ascending dose study (see IB for details) 30 healthy male subjects received single doses of AZD4017 followed by repeated doses of 75 mg once daily up to 900 mg twice daily for 9 days. The expected inhibition on 11 $\beta$ -HSD1 enzyme activity in liver measured by prednisolone generation in plasma after an oral prednisone challenge as well as on urinary GC metabolites was observed. An activation of the HPA axis was also indicated as an increase in both adrenocorticotrophic hormone (ACTH) and dehydroepiandrosterone sulphate levels while cortisol and testosterone levels were unchanged. A few subjects had transient increases in ALT and AST at 1-1.5xULN. One subject taking 1200mg once daily experienced an increase in ALT to 3x ULN. In all cases, liver transaminases returned to baseline on withdrawal of study drug. There is **no clear relationship with plasma exposure as the subjects with the highest ALT did not have the highest plasma area under the curve of either AZD4017** or the glucuronic acid metabolite.

In a Phase IIa trial of subjects with raised intraocular pressure, 7 subjects receiving 200mg AZD4017 once daily and 19 subjects receiving 400mg AZD4017 twice daily for up to 28 days, **no deaths or SAE were reported**; in the group receiving AZD4017 400 mg twice daily three subjects had ALT between 1 and 1.5x ULN, four subjects had AST between 1 and 1.5x ULN, two subjects had gamma-glutamyl transferase between 1 and 1.5x ULN and one subject had GGT between 1.5 and 2x ULN. An activation of the HPA-axis was demonstrated by an increase in ACTH and dehydroepiandrosterone sulfate levels. However, cortisol and testosterone levels were unaffected. No AEs associated with these findings were reported. In the clinical studies performed so far no obvious muscle effects have been seen.

Non-clinical data and observations in previous clinical studies with similar and even higher repeated doses of AZD4017 support dose administration according to the proposed clinical study protocol. Further information regarding non-clinical data and previous clinical studies can be found in the AZD4017 IB.

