### **13.9. Determination of sample size and randomization method**

Sample size is small as this is a preliminary pilot study and the first use in this patient group. Published rules of thumb for pilot studies recommend a sample size of 12 participants per arm completing the protocol [66]. To ensure this minimum number complete the protocol we will randomise 15 per arm to allow for 20% drop-out.

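### The out-of-range laboratory count in 13.4.2.2 ignores baseline, so abnormalities present at entry are mixed with new ones in the band where the earlier liver findings lay

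*Protocol*

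**What the plan says.** Section 13.4.2.2 lists the continuous safety variables, liver function tests and eGFR among them. It then states that "numbers of patients in each group whose values exceeded ULN (or were below the lower limit of normal) during the trial will be presented". An opening qualifier limits this to variables for which such a count is suitable, and the resulting numbers are to be "corrected for exposure by 100 patient years". The sentence sets no condition on the patient's baseline value. Section 13.3 defines baseline as the last valid measurement before study medication, but this count does not use it.

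The entry limits in 6.3.2 lie above the counting threshold. Criterion 7 excludes "Alanine aminotransferase (ALT) and/or aspartate aminotransferase (AST) and/or alkaline phosphatase (ALP) > 1.5x upper limit of normal (ULN", and criterion 8 excludes "Bilirubin (total) > 1.5x ULN". A patient between 1x and 1.5x ULN can therefore be randomised. Criterion 9 excludes an eGFR below 45, so values from 45 upwards are admitted.

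Section 8.6 describes the earlier phase IIa experience at the same dose. The group in question was "19 subjects receiving 400mg AZD4017 twice daily for up to 28 days". Of these, the section reports that "three subjects had ALT between 1 and 1.5x ULN, four subjects had AST between 1 and 1.5x ULN". It does not say whether those subjects were within limits before dosing.

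Section 13.4.2.2 also plans summaries of the same variables as changes from baseline, with between-group differences and 90% confidence intervals, and the proportion passing the overall blood-safety assessment at each visit including day 0.

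**The concern.** The event threshold (1x ULN) is lower than the entry limit (1.5x ULN). Read literally, the rule counts a patient who enters at 1.3x ULN and falls to 1.1x on treatment in the same way as one who enters within limits and rises to 1.3x. Dividing by patient-years makes the result look like an incidence rate, although part of the numerator may have been there before the first dose.

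This matters because the liver findings reported for this dose are mild and lie in exactly the band that patients may already occupy at entry. Safety is the first-listed secondary objective, there is no inferential testing, and 13.4.2.2 judges safety partly on observed differences between groups. With 15 patients per arm, a few existing cases can shift such a difference noticeably.

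**Working it through.** **Inputs from the protocol**
- Patients per arm: section 13.9 says "we will randomise 15 per arm to allow for 20% drop-out", from 12 completers. Check: 12 / (1 - 0.20) = 15. The stated figure reproduces.
- Treatment period: 35 days, with follow-up at least 7 days later (5.2).
- Earlier findings (8.6): ALT 3/19 = 15.8%, AST 4/19 = 21.1%. Scaled to 15 patients: 15 x 3/19 = 2.4 and 15 x 4/19 = 3.2.

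**Assumptions, not in the documents**
- Share of entrants above ULN at baseline: b = 10%, 20% or 30%.
- Those patients stay above ULN.
- New-onset probability among the others: q = 3/19 or 4/19 on active, and 0 on placebo (5% as a variant). Using the earlier proportions as new-onset rates is itself an assumption.
- All 15 patients per arm are observed, and arms are independent binomials.

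**Weight of one existing case in the rate**
- Over 35 days: 15 x 35/365.25 = 1.44 patient-years per arm. One patient adds 100/1.44, about 70 per 100 patient-years.
- Over 42 days: 15 x 42/365.25 = 1.72 patient-years. One patient adds about 58.

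**No drug effect.** Both counts are Binomial(15, b).

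| b | Expected existing cases per arm | P(active higher by 2 or more) | P(active higher by 3 or more) |
|---|---|---|---|
| 10% | 1.5 | 17% | 6% |
| 20% | 3.0 | 24% | 12% |
| 30% | 4.5 | 27% | 16% |

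**True drug effect.** Under the stated rule a patient is counted with probability b + (1-b)q. Under a new-onset count the probability is (1-b)q. Example for ALT, b = 20%: active 0.20 + 0.80 x 0.158 = 0.326, or 4.9 of 15, against 0.20, or 3.0 of 15, on placebo. The new-onset count is 15 x 0.80 x 0.158 = 1.9 against 0.

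| b | ALT expected, stated rule (active v placebo) | ALT expected, new onset | P(active no higher), ALT: stated rule / new onset | P(active no higher), AST: stated rule / new onset |
|---|---|---|---|---|
| 10% | 3.6 v 1.5 | 2.1 v 0 | 21% / 10% | 13% / 4% |
| 20% | 4.9 v 3.0 | 1.9 v 0 | 28% / 13% | 20% / 6% |
| 30% | 6.2 v 4.5 | 1.7 v 0 | 33% / 17% | 26% / 9% |

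**Variant with 5% new onset on placebo.** For ALT the chance that active is no higher is 33/37/40% under the stated rule and 27/30/33% with a new-onset count. The gain remains but is smaller.

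**The case against.** The strongest reply is that this is one supplementary table. The same section gives liver tests as changes from baseline, by arm, adjusted and unadjusted, with 90% intervals. That analysis is placebo-controlled and refers to baseline, and at this sample size it is more informative than a dichotomy. The pass proportion at day 0 shows pre-treatment status at panel level. Abnormal laboratory findings can also be recorded as adverse events (11.1). All of this stands, so a reader who infers that the trial cannot assess liver safety goes too far. Two gaps remain: mean changes do not show which patients newly crossed a limit, and pass or fail is one overall judgement on the blood panel.

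Randomisation is 1:1, so existing cases balance on average. That also stands: a reading of systematic bias is not supported.

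A reader might take the chance of a gap of 2 or more in either direction (35/49/55%) as the chance of a false signal. It is two-sided. Only the half in which active is higher mimics harm, and even that rests on an assumed prevalence.

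A reader might also treat 3/19 and 4/19 as established drug effects. Section 8.6 gives neither baseline values nor a placebo comparison for those counts.

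HbA1c is on the variable list and could be above a normal limit before dosing in this population. However, the sentence restricts the count to where it is applicable, which already leaves room to omit HbA1c.

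Finally, 13.10 requires a statistical analysis plan before unblinding, and shift tables are often specified there. That would excuse silence. Here the protocol states a counting rule, and followed as written it mixes two kinds of case. An analysis plan could refine the rule without contradiction, but nothing in the protocol requires it to.

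**Conclusion.** The point holds for this tabulation. The count in 13.4.2.2 cannot separate new abnormalities from those present before dosing, because its threshold is below the entry limit and baseline is not used. Under the assumptions above, existing cases alone put active ahead by 2 or more patients in 17 to 27% of trials. With true ALT onset of 3/19 on active and none on placebo, the stated rule about doubles the chance that active looks no worse than placebo (21/28/33% against 10/13/17%).

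These figures are illustrative. They depend on an assumed 10 to 30% baseline prevalence, on those patients remaining above ULN, and on reading the earlier proportions as new onset. Some noise remains after any fix, since the counts are small. The consequence is dilution and chance imbalance in one descriptive table, partly offset by other planned summaries. It deserves correction because the correction is nearly free, not because the safety assessment fails without it.

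**What to change.** In 13.4.2.2, replace the count with this: per arm, the number of patients within limits at baseline (as defined in 13.3) who go out of limits after the first dose, over the number within limits at baseline. Add a table of baseline category by worst post-dose category for each analyte, including patients already out of limits at baseline, so that worsening among them stays visible.

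The cost is one sentence and one table. Section 9.2.2.5 already collects the liver tests at screening, baseline, days 7, 28 and 35, and follow-up, so no new data are needed and patient management is unaffected. The price is a smaller denominator for the count: at the assumed prevalences, about 13.5, 12 or 10.5 patients per arm (15 x 0.90, 0.80, 0.70) instead of 15.

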### 5.2. Study duration

The protocol treatment duration is 35 days with follow-up visit at least 7 days after the last treatment dose.

Skin, plasma, serum and 24 hour urine samples will be stored for future biochemical analyses but storage will not exceed 5 years after the end of the trial. At 5 years after the end of the trial any residual samples will either be destroyed or placed in an approved Research Tissue Bank.

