#### **6.5. Withdrawal criteria**

Participants are at any time free to withdraw from study (IMP and assessments), without prejudice to further treatment (withdrawal of consent) at any point. Such participants will always be asked about the reason(s) and the presence of any AE. Participants are not under obligation to give a reason for withdrawal. If possible, they will be invited to attend a follow-up visit, ideally, at least 7 days after stopping the IMP. They will undergo the follow-up visit safety measurements and be formally discharged by telephone. Any AE will be followed up wherever possible and all remaining IMP should be returned by the participant.

Should the participant need to be withdrawn from the active treatment phase of the study between study visits for safety reasons e.g. serious adverse event (SAE) or laboratory abnormalities, study medication will be stopped immediately. If withdrawn from IMP, participants will be free to complete the remaining protocol if they choose to do so unless deemed clinically unfit by the CI, in which case they will be withdrawn from the remainder of the protocol.

IMP withdrawal criteria are as follows:

- 1) Participant decision. The subject is at any time free to discontinue treatment, without prejudice to further treatment
- 2) The participant has a clinically significant or serious AE that would not be consistent with treatment continuation, as determined by the CI or the participant; including but not limited to hospitalisation or disability, requirement for medical or surgical intervention to prevent

hospitalisation or disability; or abnormalities of liver, muscle or thyroid function that are considered unacceptable by the CI

3) Hepatotoxicity: ALT and/or ALP and/or AST >2.5x ULN or bilirubin >2x ULN. This is in keeping with Common Terminology Criteria for AE (v5.0) Grade 2 recommendations from the National Institute of Health.

4) Renal toxicity: eGFR <45

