Blood samples will be taken at screening, baseline, days 7, 28, 35 and follow-up to monitor HbA1c, lipids, liver, kidney, thyroid and adrenal function.

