#### 9.2.2.5. Blood tests

Blood samples collected at screening, baseline, study Visits 3 (day 7), 4 (day 28), 6 (day 35) and follow-up (day 42 onwards) will be analysed immediately through the Leeds Teaching Hospitals NHS Trust Pathology Service or processed and stored for future research.

Blood samples at each of these visits will evaluate HbA1c (mmol/mol) and lipids [total and high density lipoprotein cholesterol and triglycerides (mmol/l)] for T2DM disease markers and FBC [haemoglobin (g/l), white cells and platelets ( $\times 10^9/\text{l}$ ), red cells ( $\times 10^{12}/\text{l}$ ), mean corpuscular volume (fl), haematocrit (%/100), mean corpuscular haemoglobin (pg), mean corpuscular hemoglobin concentration (g/l) and red blood cell distribution width (%)], LFT

[ALT, AST and gamma-glutamyl transpeptidase (iu/l), ALP (U/l), albumin (g/l) and bilirubin (umol/l)], eGFR (ml/min/1.73m^2), U+E [sodium, potassium and urea (mmol/l) and creatinine (umol/l)], adrenal [testosterone (nmol/l) and dehydroepiandrosterone sulphate (umol/l)] and thyroid [thyroid stimulating hormone (mIU/l) and free thyroxine (pmol/l)] function (AZD4017 safety markers). CK (iu/l) will also be measured at the screening visit. Samples will be collected by authorised research nurses.

Results will be sent to the CI or authorised delegated personnel for immediate monitoring signature and dating. Signed and dated result reports will be stored with the patient's medical notes for each visit and recorded in the CRF as pass or fail.

Blood will also be taken at baseline and day 35 for separation to serum and plasma and stored at -80°C in the WTBB designated storage area for plasma AZD4017 detection and future studies (up to 5 years). At 5 years after the end of the trial any residual samples will either be destroyed or placed in an approved Research Tissue Bank.

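### Counts of patients with out-of-range laboratory values are scaled per 100 patient-years, although laboratory status is known only at four post-baseline draws (minor reporting point)

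*Protocol*

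**What the plan says.** Section 13.4.2.2 of the protocol starts from patient counts: "Where applicable, numbers of patients in each group whose values exceeded ULN (or were below the lower limit of normal"). It then says that these counts "during the trial will be presented, corrected for exposure by 100 patient years". The same section applies a patient-year correction to adverse events, in addition to numbers and percentages of subjects.

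The blood schedule is in section 8.6: "Blood samples will be taken at screening, baseline, days 7, 28, 35 and follow-up to monitor HbA1c, lipids, liver, kidney, thyroid and adrenal function". Section 9.2.2.5 and Tables 1 and 2 agree with it. Section 5.2 sets the length of observation: "The protocol treatment duration is 35 days with follow-up visit at least 7 days after the last treatment dose".

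Section 6.5 stops study drug on some of the same analytes, for example "Hepatotoxicity: ALT and/or ALP and/or AST >2.5x ULN or bilirubin >2x ULN", and also on eGFR. It lets patients who are off drug continue the remaining visits if they wish and are clinically fit.

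Section 13.4.2.2 also plans by-group summaries of each continuous laboratory variable at each timepoint, and the proportion passing an overall blood-safety assessment by visit and group.

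**The concern.** A rate per patient-year is interpretable when events are ascertained over the time in the denominator. Here the numerator is a yes/no state per patient, seen on four days after baseline. The longest gap, day 7 to day 28, is 21 of 42 days, and nothing is measured within it. A patient abnormal at one draw and a patient abnormal at all four each count once.

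The count is also not limited to new abnormalities. Section 6.3.2 admits liver enzymes and bilirubin up to 1.5 times the upper limit, and section 6.3.1 admits HbA1c up to 11%. An analyte raised before dosing would be presented as if it had occurred under exposure.

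Two consequences follow. The level of the rate depends on how often blood is drawn. It also depends on early stopping, because stopping shortens the denominator. Some stopping is triggered by the same analytes, so one abnormal draw can both enter the numerator and cut the denominator.

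**Working it through.** **Inputs.** There are 15 patients per arm (section 13.9), 35 days on treatment and at least 42 days in all (section 5.2), and post-baseline draws on days 7, 28, 35 and about 42 (sections 8.6 and 9.2.2.5). A year is taken as 365.25 days. The protocol states no rate. Its only calculable figure behind the denominator is the arm size: section 13.9 takes 12 completers and says "we will randomise 15 per arm to allow for 20% drop-out". 12/(1 − 0.20) = 15 reproduces it.

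The denominator may be days on treatment or total follow-up, so both are shown.

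**1. Scale.**
- On treatment: 15 × 35/365.25 = 1.437 patient-years. One affected patient (1/15 = 6.7%) gives 100/1.437 = 69.6 per 100 patient-years.
- Total follow-up: 15 × 42/365.25 = 1.725 patient-years. One affected patient gives 100/1.725 = 58.0.
- An analyte already out of range in all 15 before dosing (assumed, for illustration) gives 1500/1.437 = 1,044 on the on-treatment scale, although nothing new occurred.

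**2. Draw density, completer against a patient who stops at day 7 and leaves.** Draws and days are taken from the same window.
- Total follow-up, with a follow-up draw 7 days after stopping: 4/42 = 0.095 against 2/14 = 0.143 draws per day, a ratio of 1.5.
- On treatment only: 3/35 = 0.086 against 1/7 = 0.143, a ratio of 1.67.

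**3. Effect on an arm's rate, same number affected.** Suppose 3 of 15 stop at day 7 and leave after a day-14 follow-up.
- Patient-days: 12 × 42 + 3 × 14 = 546, against 15 × 42 = 630 with no early leavers.
- Inflation: 630/546 = 1.154, about 15%.
- With 3 of 15 affected, the rate moves from 300 × 365.25/630 = 174 to 300 × 365.25/546 = 201 per 100 patient-years, while the percentage stays at 20%.
- If those three attend every visit to day 42, the denominator remains 630 and the ratio is 1.

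**4. The same case with a fixed chance p of abnormality at each draw (assumed, draws independent).** The leavers now also lose draws, so fewer of them are expected to be counted.
- Expected patients affected with no leavers: 15 × [1 − (1 − p)^4]. With three leavers: 12 × [1 − (1 − p)^4] + 3 × [1 − (1 − p)^2].
- p = 0.05: 2.78 over 630 days = 161; 2.52 over 546 days = 168; ratio 1.04.
- p = 0.10: 5.16 over 630 = 299; 4.70 over 546 = 314; ratio 1.05.
- p = 0.20: 8.86 over 630 = 513; 8.16 over 546 = 546; ratio 1.06.

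So 15% applies when the number affected is unchanged, as with persistent abnormalities. Under independent draws the effect is 4% to 6%.

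**The case against.** Most of the case against concerns size, and much of it stands.

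- **Shared schedule.** Both arms are sampled on the same days, so spacing shifts the level of the rate far more than the difference between arms. Only differential early stopping affects the comparison appreciably.
- **Patients may stay on.** Section 6.5 lets patients off drug complete the visits, and section 8.9.1 withdraws nobody for non-compliance. On total follow-up the early-stopping effect then disappears.
- **No decision hangs on it.** Section 13.2 makes the analysis descriptive throughout, section 13.4.2.2 rules out inferential testing, and the stopping limits in section 6.5 act on individual values.
- **Other displays exist.** The continuous summaries and the pass proportions by visit cover part of the ground. Neither gives the number of patients outside the limits for each analyte.
- **The inflated scale is not specific to laboratory values.** One patient in 15 becomes about 70 per 100 patient-years for an adverse event too, so scale alone cannot justify treating the two differently. The difference is ascertainment: adverse events are asked about for the whole interval between visits, whereas laboratory status is not known between draws.

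A reader might infer a 2.5-fold difference in draw density for early stoppers, from 4/35 against 2/7. That counts the off-treatment follow-up draw but divides by on-treatment days, which the protocol does not prescribe. A 19% inflation (525/441) likewise divides by on-treatment days only, whereas a count taken over the whole trial includes the follow-up draw. That the protocol leaves exposure undefined is no fault in itself, since the analysis plan may define it.

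**Conclusion.** The point holds as a minor one. Section 13.4.2.2 fixes a patient-year scale for a count that is not an incidence: the state is seen at four draws, each patient counts once, and baseline abnormalities are included. One patient in 15 is shown as 58 to 70 per 100 patient-years.

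The distortion between arms is modest and conditional. It is about 15% for the same number affected if 3 of 15 in one arm stop at day 7 and leave after a day-14 follow-up, with none leaving early in the other. It is 4% to 6% under an assumed independent 5% to 20% chance of abnormality per draw. It is nil on total follow-up if all visits are completed. The stopping pattern and the per-draw chances are assumptions; the protocol gives neither.

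A reader might go further and conclude that the safety comparison is biased or that patient monitoring is weakened. The documents do not support that: the display is descriptive, and no stopping rule or formal test uses the rate.

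**What to change.** In section 13.4.2.2, remove the patient-year correction from the sentence on laboratory limits. In its place give, by arm and for each analyte:

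- n/N (%) of patients outside the limit at each scheduled visit, where N is the number with a sample at that visit;
- n/N (%) with any post-baseline value outside the limit, among patients with at least one post-baseline sample;
- the number of post-baseline samples, and whether the value was already out of range at baseline.

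Keep exposure-corrected rates for adverse events only.

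The cost is a wording change. All the data are already collected, and the calculations are simpler than those planned. The small loss is one exposure-scaled display. The per-analyte counts would add what the overall pass proportion and the continuous summaries do not provide.
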